## Limitations and alternative methods considered

The AWARE curriculum does not include specific references to marijuana (although it is discussed if a participant brings it up during a session), due to focus group feedback indicating that these young adults are not interested in attending a program that addresses their marijuana use. Nonetheless, our pilot work found positive intervention effects on motivation to change marijuana use among lower severity users [1], and we plan to examine intervention effects on marijuana use and related attitudes in this larger evaluation. The study is also limited by its exclusively reliance on self-report data, although this is typical for most research of this nature. Finally, although the evaluation is being conducted in agencies located in two distinct areas of Los Angeles County, it is unclear whether results will generalize to other agencies located in other geographic regions.

We initially considered a design in which individuals would be randomly assigned to condition within agency. However, we decided against this design given concerns on the part of the research team and drop-in center staff about implementation challenges (e.g., clients perceiving that they were being refused services that other clients were getting) and the strong potential for contamination across conditions. A group-randomized design was a much better option for this evaluation in that it addressed these concerns. We are maximizing the comparability of the intervention and control groups by having each drop-in center serve as both intervention and control site on an alternating basis, as well as using the same procedures at each drop-in center to identify and recruit participants for the study. In addition, once data are collected, we will conduct preliminary analyses to determine whether the intervention and control groups differ on baseline characteristics. This step is necessary despite randomization as randomization is not occurring at the individual level. In the pilot evaluation, which used the same procedure, there were no significant baseline group differences on demographic characteristics. However, any observed differences will be controlled for in all analyses testing intervention effects with the addition of model covariates. If we observe considerable differences in the intervention and control groups that cannot be adequately accounted for with the addition of model covariates, we will develop analytic weights using propensity methods to balance the groups. We will also control for any within-agency effects by including agency as a fixed effect (dummy coded) within the models.

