### Procedures

This study is using a form of group-randomized design [44, 45], with crossover of conditions and groups to avoid problems of power reduction associated with conventional group randomization [46]. The unit of analysis is the individual, but individuals are assigned to groups based on the agency where they are seeking services. Specifically, young adults at three drop-in centers serving young people experiencing homelessness are either in the intervention condition (*N* = 200) or control condition (*N* = 200). Drop-in centers are typically a first stop resource for these youth to address their basic needs for food and hygiene, and a place where they can go during the day to receive services, or get connected with services outside the drop-in centers, to address their higher-level needs [41]. Drop-in centers typically try to break down barriers and take a “come as you are” approach to engaging youth in available services [42]. Participants in the intervention condition receive the AWARE program, whereas participants in the Usual Care control condition have access to the full range of programs and services that are already available at the drop-in center (these programs and services are available to intervention participants as well). In addition, all participants receive an HIV informational brochure that discusses the connection between AOD use and HIV risk, and a Community Resource Guide that lists free or low-cost AOD and HIV-related services in the study area.

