Recruitment occurs in a series of 16-week cycles, with the three drop-in center sites alternating across cycles in serving as the intervention site or control site (see Fig. 1). Recruitment is done by advertising the study at the drop-in centers, and through soliciting volunteers during recruitment visits. Individuals sign up on a sign-in sheet each day to participate in the study. Depending upon the number who sign up, they are randomly selected from the pool of interested individuals and screened for eligibility. Eligible participants provide written consent and complete a baseline scannable self-report survey, which takes approximately 30 min, and is completed in the presence of a staff member who can provide assistance if needed. Participants in both conditions are recruited during the first 8 weeks of each cycle, until our target enrollment number for that cycle is reached, which leaves the remainder of the cycle as a “wash out” period to reduce the likelihood of contamination across conditions. The four-session AWARE program is delivered four times during each 16-week cycle, allowing intervention participants multiple opportunities to complete all sessions. Figure 2 depicts participant flow through the study, and Fig. 3 contains a SPIRIT (Standard Protocol Items: Recommendations for Interventional Trials) flow diagram of the RCT schedule of enrollment, interventions, and assessments.

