### Analytic plan

We will compare the intervention and control groups on each of the primary and secondary outcomes with a multilevel modeling approach using SAS PROC MIXED for continuous outcomes (e.g., past month quantity-frequency of alcohol use; proportion of protected sex acts; past month income) and PROC GLIMMIX for categorical or count outcomes with overdispersion and/or zero-inflation accounted for as needed in the modeling approach (e.g., any past month heavy drinking; number of sex partners; number of jobs in past 3 months) using restricted maximum likelihood estimation. Outcomes will be tested at each time point (3-, 6-, and 12-months) and longitudinal analyses will be used to test for differences in change over the 12-month period. Although testing at each time point provides estimates of the intervention effect at that time, the longitudinal analysis will capture patterns of change over time, that is, whether the average change on outcomes within each group produce parallel lines over time vs. lines with different slopes vs. non-linear patterns. We will explore dose–response relationships given that participants voluntarily choose to attend 1 to 4 program sessions. Although we consider any attendance as receiving the intervention, attending more sessions may be associated with better outcomes [86]. In addition, we will conduct an analysis to explore whether observed program effects differ by gender or substance use severity (defined by a score of 3 or higher on the GAIN-SS) [83] by estimating separate models for each group and/or by including an interaction term in the models.

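### Condition is assigned by center within cycle, but agency dummies are the only design term stated; unless a center-by-cycle effect is fitted, standard errors will be too small whenever the within-cell correlation is above zero.

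*Protocol article*

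**What the plan says.** The Procedures section of the protocol article sets out enrolment in successive cycles of 16 weeks each and has "the three drop-in center sites alternating across cycles in serving as the intervention site or control site". It also states that both conditions recruit in each cycle. On the unit of analysis it says: "The unit of analysis is the individual, but individuals are assigned to groups based on the agency where they are seeking services". The crossover is justified as a device "with crossover of conditions and groups to avoid problems of power reduction associated with conventional group randomization". Planned enrolment is 400, with 200 per condition, at three centers.

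The second Analytic plan section, which follows the secondary outcomes, compares the groups on each primary and secondary outcome "with a multilevel modeling approach using SAS PROC MIXED for continuous outcomes" and PROC GLIMMIX for categorical or count outcomes. It does not say what the levels or random effects are.

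The section on limitations and alternative methods acknowledges that individuals are not the unit of randomization, then gives the term for place: "We will also control for any within-agency effects by including agency as a fixed effect (dummy coded) within the models". Baseline covariates, and propensity weights if needed, are planned for group differences. No term for cycle, calendar time or the center-by-cycle cell is mentioned.

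**The concern.** Condition does not vary within a center-by-cycle cell. After agency dummies are fitted, the AWARE comparison is a comparison of cells with other cells of the same center. The relevant error is therefore the cell-to-cell variation within a center, and agency dummies leave that variation in place. Crossover removes the penalty from stable center differences, but not the penalty from people in one cell resembling each other.

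Some resemblance is plausible. Participants in a cell share season, staff and the services on offer at the time, and in AWARE cells they also share small-group sessions meant to work through group norms. If the model treats them as independent given agency, confidence intervals are too narrow and p-values too small for the primary and secondary outcomes alike.

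The second strand is calendar time. With three centers alternating, a cycle cannot be evenly split by center, so cycle and condition are partly confounded and no cycle term is stated.

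**Working it through.** The article gives no power, alpha, target effect or ICC, so there is no figure to reproduce.

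**Inputs.** From the article: N = 400, 200 per condition, three centers, alternation by cycle. Assumed, because the text does not give them: two-sided alpha 0.05; 4, 6 or 8 cycles; equal cell sizes; within-cell ICC (beyond agency) of 0 to 0.05; strict alternation, since Fig. 1 is not shown.

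**Formulas.** Cell size m = 400 / (3 × cycles). Design effect DE = 1 + (m − 1) × ICC. True SE divided by the SE from a model with no cell effect = √DE. Actual type I error = 2 × [1 − Φ(1.96 / √DE)].

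**One case in full.** Four cycles give 12 cells, so m = 400/12 = 33.3. At ICC 0.02, DE = 1 + 32.3 × 0.02 = 1.65, √DE = 1.28, and 2 × [1 − Φ(1.96/1.283)] = 12.7%.

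| Cycles | Cells | m | ICC | DE | SE ratio | Type I error, formula | Type I error, simulated |
|---|---|---|---|---|---|---|---|
| 4 | 12 | 33.3 | 0.01 | 1.32 | 1.15 | 8.8% | 8.3% |
| 4 | 12 | 33.3 | 0.02 | 1.65 | 1.28 | 12.7% | 13.3% |
| 4 | 12 | 33.3 | 0.05 | 2.62 | 1.62 | 22.6% | 22.6% |
| 6 | 18 | 22.2 | 0.01 | 1.21 | 1.10 | 7.5% | 7.9% |
| 6 | 18 | 22.2 | 0.02 | 1.42 | 1.19 | 10.1% | 10.1% |
| 6 | 18 | 22.2 | 0.05 | 2.06 | 1.44 | 17.2% | 17.6% |
| 8 | 24 | 16.7 | 0.01 | 1.16 | 1.08 | 6.8% | 6.6% |
| 8 | 24 | 16.7 | 0.02 | 1.31 | 1.15 | 8.7% | 8.8% |
| 8 | 24 | 16.7 | 0.05 | 1.78 | 1.34 | 14.2% | 13.9% |

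The simulation used 4,000 runs per setting, a continuous outcome, no true effect, and an individual-level regression on condition plus agency dummies. At ICC 0 it rejected 4.7-5.3%, so there is no inflation there. A regression of cell means on condition, agency and cycle rejected 4.2-5.6% in every setting run.

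**Calendar time.** With three alternating centers, each cycle has two centers in one condition and one in the other. Suppose outcomes differ by δ between odd and even cycles. With equal recruitment by center, two centers show −δ and one shows +δ, so the bias is (−δ − δ + δ)/3 = −δ/3; δ = 0.3 SD gives 0.10 SD in size. For a linear drift totalling 0.3 SD, the bias is one third of the change per cycle: 0.3/3/3 = 0.033 SD with 4 cycles, 0.3/5/3 = 0.020 with 6, 0.3/7/3 = 0.014 with 8, and zero for an odd number of cycles. With random cycle-wide shifts worth 2% of the variance and no cell effect, the agency-only regression rejected 6.2-7.5%, against 4.8-5.4% for cell means with cycle terms.

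**The case against.** The strongest reply is that the article does not say agency dummies are the whole model. It promises a multilevel approach and says that agency is also included. A random effect for the cell is neither stated nor excluded, and the details may sit in a full protocol or analysis plan that is not shown. This stands in part. A reader might infer that the plan leaves out every cell-level effect and that its standard errors are certainly too small. The documents do not support that: the levels are unnamed, and the regression simulated here is what results if no cell effect is fitted, not a transcription of the stated model.

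The point is still more than missing detail. The article says how within-agency effects will be controlled, and the term it names cannot do that for correlation within a cell. With follow-up at 3, 6 and 12 months, the participant is at least as natural a reading of the random level, and a participant intercept would not capture cell clustering.

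Three further objections stand as limits on size. The ICC and number of cycles are assumptions, and the 23% figure needs both ICC 0.05 and only four cycles. Binary, count and zero-inflated outcomes were not simulated. The 0.10 SD period bias is close to a worst case: odd/even alternation repeats every 32 weeks and does not follow a yearly season. Concurrent recruitment of both conditions gives partial protection, and enrolment balanced 1:1 by condition within each cycle would remove this bias.

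The planned covariates and propensity weights can reduce differences in composition between cells. They do not model correlated errors.

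**Conclusion.** The concern holds in conditional form. The unit of assignment is the center within cycle, the only design term stated is agency, and agency dummies leave the cell-to-cell variation that carries the treatment contrast. If no cell-level effect is fitted and the within-cell ICC is above zero, standard errors are too small: by 8-15% relative to the model's own at ICC 0.01, 15-28% at 0.02 and 34-62% at 0.05 (8 down to 4 cycles). Type I error is then about 7-9%, 9-13% and 14-23%. These figures rest on 400 participants in equal cells, 4 to 8 cycles and strict alternation; at ICC 0 nothing is lost.

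Calendar time is secondary. A period shift can enter the effect in part, up to one third of an odd/even-cycle difference if centers recruit equally, and much less under smooth drift. A reader might take 0.10 SD as the expected bias; the documents give no basis for a shift of that form or size.

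**What to change.** State the model in full. Keep agency as a fixed effect, add cycle as a fixed effect, and add a random intercept for each agency-by-cycle cell, plus one for participant in the longitudinal models. Keep the cell effect in the model whatever its estimate. Use Kenward-Roger or Satterthwaite degrees of freedom where the procedure offers them. Check each main result against an analysis of agency-by-cycle means. That cell-mean analysis is what held its level in the simulation; the mixed model itself was not simulated.

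The change needs a few lines of wording and code and no new data. The cost is precision. With 200 per condition and independent observations, 80% power corresponds to d = 0.28. With the design effects above this becomes about 0.30-0.32, 0.32-0.36 and 0.37-0.45 at ICC 0.01, 0.02 and 0.05, by normal approximation.

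Cycle terms cost a little more. With a 2:1 split by center and an even number of cycles, condition coded ±1/2 has variance 1/4 before and 1/4 − 1/36 = 8/36 after cycle is removed, so the variance of the effect rises by 9/8 and its SE by about 6%. In the cell-mean analysis the residual degrees of freedom are 5, 9 and 13 for 4, 6 and 8 cycles, which widens intervals further.

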## Discussion

AWARE is a brief MI intervention designed to reduce AOD use and sexual risk behavior among young adults experiencing homelessness. The prior AWARE pilot study found short-term effects on AOD use and sexual risk behavior [1], and this full-scale clinical trial provides a critical next step by evaluating its effectiveness over a 12-month period in a larger and more diverse sample. It will also examine whether AWARE, by reducing AOD use, has positive effects on secondary outcomes such as health-related quality of life and social stability. This is important as this population faces numerous challenges in the areas of mental and physical health, establishing and maintaining positive supportive connections, as well as finishing their education, securing employment, and transitioning to stable housing. There is a critical need for risk reduction programs for young people experiencing homelessness that are effective, acceptable and feasible to both participants and service providers.

## Data Availability

Once collected, deidentified data from this study will be available from the corresponding author on reasonable request 1 year after all aims of the project are completed. Requestors of data will be asked to complete a data-sharing agreement that provides for 1. a commitment to using the data only for research purposes and not to identify any individual participant; 2. a commitment to securing the data using appropriate computer technology; and 3. a commitment to destroying or returning the data after analyses are completed.

## Abbreviations

AOD: Alcohol and other drug
HIV: Human immunodeficiency virus
MI: Motivational interviewing
STD: Sexually transmitted disease
